### Intervention condition

The *Atmiyata* intervention has been described extensively elsewhere [13]. Briefly, *Atmiyata* is a complex psychosocial intervention involving two-tiers of community volunteers for identification and support to people in distress and with symptoms of common mental disorders. The first tier consists of community volunteers called *Atmiyata* Mitras who are from different caste and religion-based sections of the village, trained to identify persons in mental distress. The second tier consists of *Atmiyata* Champions, who are important community members (e.g. former teachers, community leaders) with leadership and communication skills and are well-known and approachable in their village. Champions are trained to identify and provide structured counseling to persons with significant mental distress, including the ones referred by Mitras. Given the social barriers based on caste, gender, religion, the identification and support by Champions and Mitras ensure equitable reach and improves coverage of the intervention across the entire village.

In the *Atmiyata* pilot intervention in the state of Maharashtra in 2013–2015, Champions and Mitras were trained by the project team. In this study, the *Atmiyata* Gujarat program, where the target population is substantially larger, Champions are identified and trained by Community Facilitators (CF) who typically have a master’s degree in social work or related fields, are locally based and aware of community dynamics. CFs first map their allotted villages, then identify and recruit the Champions, train them and provide ongoing mentoring support to Champions. The CFs are recruited, trained and mentored by Project Managers (PM). Each PM supports 7–8 CFs. Each CF supports 40–50 Champions (1 per 1000 population), and each Champion has 4–5 Mitras. The principal Investigator (PI) monitors and supports the PMs (Fig. 2).

**Fig. 2 Fig2:**
[figure not shown]
*Atmiyata* Implementation team structure

Mitras receive 4 h of training from a Champion based in a particular village. Champions receive 40 h of training over 3 weeks, at a central location in the block or village area. PMs and CFs receive 55 h of training over 5 weeks, with additional 8-h sessions on how to be a master-trainer. The methodology of the training is interactive, reflective and participatory.

The Champions are trained: (i) to identify persons with CMD and provide evidence-based 4–6 counseling sessions; (ii) to raise community awareness on social issues by ‘narrow-casting’ four films; 10-min films dubbed in Gujarati on commonly experienced social issues in the community such as unemployment, family conflict, domestic violence, and alcoholism. Films are developed to build community mental health awareness and were not designed for training purposes or for intervention delivery related to counselling or symptom reduction. The films are shown to community members in the village where the Champions reside, typically in a public space in the village. Champions show these films in a small group of 3 to 4 people at communal meeting places in a village such as a temple, at a farm or Champion’s house [32].; Champions also (iii) make referrals of persons with severe mental disorders to mental health services offered within the public health system when required, and (iv) enable access to social benefits for persons with mental health problems, such as government schemes for paid work opportunities.

Counseling sessions by Champions are based on three evidence-based techniques used in prior and similar task-sharing programs [33, 34]: active listening, activity scheduling and problem-solving techniques. The training includes basic skills of empathy, non-judgemental behaviour, rapport building, verbal and non-verbal communication and creating a safe environment to build skills for ‘active listening’. Activity scheduling techniques enable individuals to explore reasons why they have been avoiding activities and schedule pleasurable and valuable activities to resume day to day routine [35, 36]. Problem-solving techniques are used for a positive orientation towards the problem which enables viewing problems as solvable, and as opportunities to learn and change. Champions are trained to deliver 4–6 sessions of counseling over a period of 6 to 12 weeks, with no set time between sessions. Each session lasts 20 to 40 min based on mutual agreement between the Champion and the participant. The number of sessions delivered to the participant is also left to mutual agreement between the Champion and the participant. As this is an implementation research study, we aim to assess what happens when the intervention is implemented in ‘real-life’ settings where the number, duration, and frequency of sessions will vary between the different provider (Champion) and participant dyad. We therefore provide broad guidelines and recommendations on the number, duration and frequency of sessions to Champions (e.g. a range of sessions from 4 to 6 sessions, duration from 20 to 40 min, and period of 6–12 weeks) which both mimics what is likely to happen in real-life clinical settings and allows us to explore the possibility of dose-response effects in the study. Champions deliver the intervention at the participant’s home or immediate surroundings at a location preferred by the participant (e.g. champion’s home, a community place such as village hall, temple, etc.). Thus, participants do not have to travel to receive the intervention. The delivery of intervention is in the Gujarati language.

Supervision and mentoring are important components of our Intervention [13]. In the *Atmiyata* intervention, the PI (who is also a clinician) is the primary supervisor of the PMs and CFs. The PMs and CFs supervise and mentor champions delivering the intervention. The PMs and CFs receive 7 days of training in the intervention with an additional 3 days of training on supervision and mentoring. These 10 days of training for CFs and PMs are supplemented through routine supervision discussions with the PI. The PMs and CFs go on to conduct a 7-day training for the Champions. CFs visit the Champions on-site once a month for hands-on mentoring sessions. During these visits, CFs discuss with Champions the counseling sessions delivered by them, check the structure of each session and troubleshoot any difficulties in using counseling techniques. CFs also help champions clarify concepts and if necessary, demonstrate counseling techniques. These monthly visits ensure the quality and fidelity of the intervention are maintained. Day-long refresher sessions are scheduled once every three months to bring Champions and CFs back together to discuss common challenges and strategies to overcome challenges in delivering the intervention.

### Adverse events

We considered adverse events as attempted suicide, self-harm or death by suicide. A protocol for reporting and recording of adverse events is provided in the Additional file 1. All team members are trained by the data manager and PI on proper identification, recording, and reporting of adverse events. All adverse events are tracked as per the protocol and reported to the Institutional Ethics Committee within 15 days of occurrence. We decided to only track the above-mentioned adverse events because *Atmiyata* provides low-intensity counseling package delivered by Champions to people with distress and CMD, and other events such as non-suicide related hospitalizations are not directly related to the service being provided. This specific definition of adverse events was agreed upon by the ethics committee advising the project on ethical considerations and documented and defined in the trial protocol.

### Comparison condition

Participants in the control condition receive Enhanced Usual Care (EUC). EUC is offered to all participants in the comparison condition who scored 3 and above on GHQ-12. EUC provides information on the impact of distress on their physical and mental health and relevant information of accessible and available public mental health care services, including services by the District Mental Health Programme (DMHP), and helplines for mental health support and domestic violence in and around Mehsana district.

The EUC conditions also has provisions for providing active support to participants in crisis. A crisis is defined as the participant revealing a recent self-harm attempt or expressing thoughts of self- harm during data collection. Such participants are encouraged to seek help immediately and the data collectors seek participant consent to inform their family member or a friend about the crisis and thus, mobilize social support to deal with the crisis.

### Sample size and power calculations

A trained lay health worker-led intervention study conducted in India reported a risk difference of 12% at follow up between intervention and control condition for the recovery of CMD patients [5, 37]. The sample size for this SW-CRCT is calculated to detect a 13% difference in CMD cases at a 3-month follow-up using GHQ-12 as a categorical measure between the intervention (58% improved) and control condition (45% improved). Assuming an intra-cluster correlation coefficient of ICC = 0.1, number of steps (t = 4), number of clusters randomized in each step (k = 14), average cluster size (m = 4), power (80%) and alpha of 0.05, a sample size of 1120 participants is needed, with approximately 56 individuals per cluster per period (Fig. 1, 3). The sample size was calculated using the “stepped wedge” function of STATA version 14 [38].

**Fig. 3 Fig3:**
[figure not shown]
CONSORT Flow chart for *ATMIYATA* SW-CRCT design *PHCs in the consort diagram refers to groups of clusters based on geographical area

### Randomization and treatment allocation

The unit of randomization in stepped wedge trials is a cluster or group of clusters, allocated to different steps. In India, PHCs serve discrete villages and hence we have used the PHC as a unit to identify discrete geographical areas consisting of all villages under a PHC. This geographical area is taken as a cluster for our study. Typically, a PHC in Gujarat covers a population of 25,000–30,000 across 12–13 villages. There are 56 PHCs in the Mehsana district, split into 4 groups (A, B, C, D), with each group consisting of all villages under 14 PHCs. These groups of clusters (A, B, C, D) are sequentially allocated to different steps at given time periods. Randomization takes place at the level of participants, all the participants are randomly selected for each period from each of these groups of clusters (A, B, C, D) as described in the recruitment section below. The administrative organization of primary health care in Gujarat ensures that the inter-PHC movement of people for health care is minimal and avoids contamination of the intervention. Since double-blinding is not possible in such psychosocial intervention trials, several other procedures are used to minimize contamination and bias. To minimize contamination due to the intervention and control village members meeting and potentially discussing the intervention, clusters are geographically dispersed. Second, the data collection team is separate from the intervention team and blind to the treatment status. Third, the data collection staff receives initial training and re-training at repeated intervals to ensure the quality of data collected.

### Recruitment

In the control condition (enhanced usual care), a screening list is generated from the district electoral roll using a systematic random sampling method with pre-decided random start and random interval, with every *n*th number from the pool being selected. We used electoral roll as it is the most complete, comprehensive and accessible national frame of residential addresses in India and electoral rolls are extensively used for drawing a random sample from the general population [39]. For each group of clusters (A, B, C, and D) electoral rolls from all the villages under 14 PHCs are included. Since the prevalence of CMD is 4–8%, according to the National Mental Health Survey, India [1], a screening list using a minimum prevalence of 4% and assuming 25% missing persons is prepared. For each group (A, B, C and D) in each period of the control condition, a screening list of 1800 participants is created and screened (GHQ-12 score of 3 and above) to achieve the target sample of 56 participants.

A different recruitment procedure is used in the intervention condition, as using structured questionnaires for identification (e.g. GHQ, PHQ) was perceived as impractical when implementing the intervention at scale and seen as stigmatizing in a community setting. Champions are trained to identify a person in their catchment area (i.e. villages) with CMD based on symptoms described by the participant during an unstructured interview. When a Champion identifies a person with CMD to whom they intend to provide 4–6 counseling sessions to, they are asked to inform their CF who in turn informs the data manager who creates a caseload list for each Champion. All caseload lists across Champions are then merged to create a master list. The master caseload list has the residential address of the persons identified by the Champion, who are then approached by the data collection team. Champions obtained verbal consent from each person before providing any personal information such as the address to the CF. CFs are trained to maintain confidentiality of this information (see the section on data storage, confidentiality below). The sample for the intervention condition is drawn from this master caseload list using a computer-generated random method. The drawn sample is screened by data collection staff using GHQ-12 (score of 3 and above) for recruiting intervention participants. This screening and subsequent baseline data collection for participants meeting the inclusion criteria is done prior to the Champion starting psychosocial counseling sessions with the participant. This process is continued until the target sample size of 56 cases is reached for each cluster and period. A different recruitment procedure for the intervention condition was chosen in order to estimate the specificity (accuracy) of ident ification of CMD cases by Champions, which is one of the secondary outcomes. Using similar recruitment procedures in both control and intervention condition (using electoral rolls) would have answered the coverage question (how many people with CMD in the community were identified by the Champion) but not allow us to assess accuracy of identification. We first want to establish whether Champions are accurately able to identify persons with CMD, before addressing the coverage question. Furthermore, we have other data to estimate the population coverage of the intervention.

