#### Specificity of identification of CMD cases

The accuracy of Champions identifying community members with CMD by Champions is assessed using the GHQ-12.

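### The secondary outcome named specificity of Champion identification can only be estimated as a positive predictive value, so one of the two stated reasons for the different recruitment is mis-stated

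*Protocol article*

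**What the plan says.** Among the secondary outcomes, the protocol article has a subsection headed "Specificity of identification of CMD cases". Its only sentence is "The accuracy of Champions identifying community members with CMD by Champions is assessed using the GHQ-12".

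The Recruitment section sets out who is tested in the intervention condition:

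- Entry to the list: "When a Champion identifies a person with CMD to whom they intend to provide 4–6 counseling sessions to, they are asked to inform their CF". The facilitator informs the data manager, and the Champions' lists are merged into one master caseload list.
- Sampling: "The sample for the intervention condition is drawn from this master caseload list using a computer-generated random method".
- Reference test: "The drawn sample is screened by data collection staff using GHQ-12 (score of 3 and above) for recruiting intervention participants".
- Stopping: "This process is continued until the target sample size of 56 cases is reached for each cluster and period".

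Control participants are drawn from the electoral roll and screened with the GHQ-12. No Champion judgement about them is described.

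The same section gives two reasons for recruiting differently under intervention. The first is that structured questionnaires for identification "was perceived as impractical when implementing the intervention at scale and seen as stigmatizing in a community setting". The second is the outcome itself: "A different recruitment procedure for the intervention condition was chosen in order to estimate the specificity (accuracy) of" CMD identification by Champions, which it calls a secondary outcome. It adds that using electoral rolls in both conditions would have answered the coverage question but not the accuracy question.

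**The concern.** Specificity is the share of people without CMD whom Champions do not flag. To estimate it, one needs people without CMD together with the Champion's verdict on each, including those the Champion passed over. The intervention sample holds only people the Champion flagged, so the required denominator is missing.

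Two things are at stake. First, a named secondary outcome could be reported as a property of the Champions' judgement when it is a different quantity, one that also moves with prevalence and sensitivity. A reader weighing scale-up could take a modest PPV for poor specificity, or take a high PPV as evidence about people who were never tested. Second, the Discussion concedes that the different recruitment strategies may confound the treatment comparison. Part of the justification for accepting that is worded in terms of a quantity the sample cannot supply.

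**Working it through.** **1. Which cells are observed.** Cross-classify Champion verdict against GHQ-12 of 3 or more.

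| | GHQ-12 ≥ 3 | GHQ-12 < 3 |
|---|---|---|
| Champion identified | TP: observed | FP: observed |
| Champion did not identify | FN: not observed | TN: not observed |

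Specificity = TN/(TN+FP), and sensitivity = TP/(TP+FN). Each needs an unobserved cell. PPV = TP/(TP+FP) needs only the observed row. Control participants do not fill the bottom row, because they carry no Champion verdict.

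**2. What the plan's own numbers identify.** The article gives no target figure for this outcome. Its total sample size reproduces as 4 groups × 5 periods × 56 = 1120. With one group crossing at each of four steps, the intervention group-periods number 4+3+2+1 = 10, giving 10 × 56 = 560 GHQ-positive intervention cases. Then PPV = 560/(number screened from the caseload list). For illustration:

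- PPV 0.5 means 560/0.5 = 1120 screened, of whom 560 are false positives.
- PPV 0.8 means 560/0.8 = 700 screened, of whom 140 are false positives.

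Sampling stops on a fixed count of positives, so all the information lies in the denominator. If only recruited participants were kept, the ratio would be 560/560 by construction.

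**3. PPV does not determine specificity.** PPV = se·p / [se·p + (1−sp)(1−p)]. Prevalence p of 4–8% is the article's figure for sizing the control screening list. Sensitivity (se) and specificity (sp) are assumed.

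| se | sp | p = 4% | p = 8% |
|---|---|---|---|
| 0.5 | 0.95 | 0.020/(0.020+0.048) = 0.294 | 0.040/(0.040+0.046) = 0.465 |
| 0.5 | 0.99 | 0.020/(0.020+0.0096) = 0.676 | 0.040/(0.040+0.0092) = 0.813 |

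The gap between specificity and PPV is 48–66 points in the first row and 18–31 points in the second. With specificity held at 0.95, PPV runs from 0.08 (se 0.1, p 4%) to 0.61 (se 0.9, p 8%).

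**4. The reverse direction.** Specificity = 1 − f(1−PPV)/(1−p), where f is the share of adults flagged. With f assumed to be 0.5–4% and p 4–8%:

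- PPV 0.2: from 1 − 0.04×0.8/0.92 = 0.965 to 1 − 0.005×0.8/0.96 = 0.996.
- PPV 0.8: from 1 − 0.04×0.2/0.92 = 0.991 to 1 − 0.005×0.2/0.96 = 0.999.

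Specificity would look high even if 80% of identifications were wrong. Recovering it needs f and p from elsewhere, and the article plans no such step.

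**5. The electoral-roll argument.** Using the control-list figures (1800 listed, 25% missing, 4% prevalence), a roll sample yields about 1800 × 0.75 × 0.96 = 1296 non-cases per group-period. That is the denominator specificity needs, provided Champion status were recorded. The same 1350 people would include only 1350 × 0.005 ≈ 7 to 1350 × 0.04 = 54 flagged people under the assumed f, a thin base for PPV. The article's statement that rolls give coverage but not accuracy is therefore reasonable if accuracy means PPV, and reversed if it means specificity.

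**The case against.** The strongest reply is that the authors use specificity loosely. They gloss it in brackets as accuracy, the subsection text speaks only of accuracy, and they set it apart from coverage. The natural reading is the share of Champion-identified people who are GHQ-12 cases, which the design does estimate. This stands: the aim is mislabelled, not empty. A reader might infer that the outcome yields nothing, and the article does not support that.

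A reader might also infer that the different recruitment was adopted solely to obtain an unobtainable quantity. The Recruitment section gives impracticality and stigma first, and that reason survives any renaming. Only the second reason is mis-stated.

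A third tempting reading is that the reported value will be 48–66 points too low. That range depends on an assumed sensitivity of 50% and specificity of 95%; at specificity 99% it is 18–31 points. The 4–8% is a survey prevalence of CMD. It is not shown to be the prevalence of GHQ-12 ≥ 3, nor that among people whom Champions assess. The article gives no formula for the outcome, so how it will be computed is not known either.

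Finally, the outcome is absent from the abstract's list, has no row of its own in Table 1, and affects neither the primary estimate nor the sample size. That limits the consequence but does not make the label correct: the subsection heading and the Recruitment section both call it specificity, and no analysis-plan wording can recover true negatives from this sample.

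**Conclusion.** The point holds as a mislabelled outcome and one mis-stated rationale. Specificity and sensitivity of Champion identification are not estimable from the sample described; PPV against GHQ-12 ≥ 3 is. This follows from who is tested and rests on no numerical assumption. The size of any gap between PPV and specificity does depend on assumed inputs: with sensitivity 50% and prevalence 4–8%, PPV is 29–47% at specificity 95% and 68–81% at specificity 99%. The correction matters because it changes what the trial may conclude about Champions' identification. It does not touch the primary analysis. Nor does it remove the recruitment bias acknowledged in the Discussion, for which the Statistical analysis section plans baseline-covariate adjustment; whether that adjustment suffices is a separate question.

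**What to change.** 1. In the secondary-outcome subsection and in Recruitment, rename the outcome as the positive predictive value of Champion identification against a GHQ-12 score of 3 or more.
2. Define it as people scoring 3 or more divided by all caseload-list persons screened. Retain everyone screened, including those scoring below 3, because sampling stops once 56 cases are reached.
3. In the recruitment rationale, replace specificity with PPV, and leave the impracticality and stigma reason as it is.
4. State that sensitivity and specificity of Champion identification are not estimable from this sample.

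The cost is wording only. No new data are needed, provided the count of caseload-list persons screened has been kept.
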